### Trial design

This is a randomized, double-blind, cross-placebo clinical trial to determine the improvement in rhinitis and asthma symptoms after dust mite exposure reduction. Participants will be randomly divided into 2 groups (group 1 and group 2). From the first day to the 8th week, the patients will apply mite baits or the placebo packages and complete questionnaires three times (V1–V3, V1 = the first day after enrolment; V2 = the fourth week plus or minus 3 days after enrolment; V3 = the eighth week plus or minus 3 days after enrolment). House sampling will be conducted twice (V1 and V3) during this period. After 4 weeks of washout, day 85 marks the beginning of the second phase of treatment.

During this period, the patients will be crossed to accept different interventions for 8 weeks. Questionnaires will be completed three times again (V4–V6, V4 = the twelfth week plus or minus 3 days after enrolment, V5 = the sixteenth week plus or minus 3 days after enrolment, V6 = the twentieth week plus or minus 3 days after enrolment), and house sampling (V4 and V6) will be completed twice again. Finally, we will conduct the questionnaire survey 4 weeks after the end of the intervention (V7, V7 = the twenty-fourth week plus or minus 3 days after enrolment). Throughout the study, the children will receive standard treatments in accordance with asthma and AR guidelines [13]. The efficacy of mite bait in reducing AR and asthma symptoms will be assessed using a visual analogue score (VAS) for rhinitis symptoms, Rhinitis Control Assessment Test (RCAT) score, Rhinoconjunctivitis Quality of Life Questionnaire (RQLQ) score, changes in the level of dust mites, drug usage for asthma and AR, Asthma Control Questionnaire-5 (ACQ-5), and frequencies of acute asthma attacks, emergency visits, and hospitalizations.

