### Intervention description

After recruitment (V0), baseline medical characteristics (name, age, sex, diagnosis of asthma and rhinitis and the allergen test report) will be collected. The subjects will be randomly divided into 2 groups. The children randomly assigned to group 1 will be placed with package A for an 8-week intervention. All HDM species reach adulthood within 3 to 4 weeks. Once mature, adult mites have a life expectancy of between 4 and 6 weeks [15]. To avoid an impact of the first intervention on the subsequent intervention, we will establish a 4-week washout period according to the growth cycle of the dust mites. After the 4-week washout period, package B will be placed for an 8-week intervention. In group 2, package B will be placed for an 8-week intervention, followed by a 4-week washout period and then package A will be placed for an 8-week intervention. Each child will undergo a total intervention period of 16 weeks, a washout period of 4 weeks, and a follow-up period of 4 weeks after the end of the second intervention. A flow chart of the study is shown in Fig. 1. At V1, V3, V4, and V6, the staff will collect indoor samples from mattresses using a glass fibre membrane, mite-clearing vacuum cleaner. The components of dust mite antigens in the collected samples will be detected via enzyme-linked immunosorbent assays. Parents will be asked to evaluate the AR and asthma symptom scores and clinical event records at V1–V7 (see the outcome indicators for details), as shown in Table 1.

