
### Sample size

Based on the assumption that a reduction of 25% in VAS scores would be of clinical significance, enrolment of 44 patients in each group is required at the 5% significance level (two-tailed), with a power of 90% to detect differences between the two groups [19]. Considering a 10% possible dropout rate, at least 49 people need to be enrolled in each group.

In this study, we will recruit 60 people for a placebo-controlled, double-blind, crossover trial. After crossover, both the placebo and experimental groups will each be increased to 60 people.

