### Procedure for unblinding if needed

When the trial is over, the number of each subject and the treatment plan received need to be checked, and the sealed distribution sequence needs to be decrypted. When unblinding, the intervention measures recorded in the assigned serial number will be checked with the drug delivery record sheet, and the results data will be classified as the test group or the control group for analysis.

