## Statistical methods

### Statistical methods for primary and secondary outcomes

SPSS 20.0 software will be used to analyse the experimental data. Descriptive statistics will be used for the following data analyses: categorical variables, namely, RCAT scores, ACQ-5 scores, drug usage for asthma and AR, and frequencies of acute asthma attacks, emergency visits, and hospitalizations via frequency tables (i.e. number of evaluable subjects, frequency and percentage for categorical values). The mean ± SD, median, minimum, and maximum will be used as continuous variables, namely, the VAS scores and RQLQ scores. One-way analysis of variance and a two-sample *t* test will be adopted for normally distributed data, and a non-parametric rank-sum test will be adopted for non-normally distributed data. Fisher’s exact and chi-square tests will be used to compare classified data, and *P* < 0.05 will be considered statistically significant.

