At present, Chinese people with allergic diseases account for approximately 30% of the total population (approximately 400 million), with allergies especially affecting those who are young [﻿28﻿]. Based on the prevalence of childhood asthma in 2010, there were 6.7 million children with asthma in China alone. Therefore, the potential consumer group for this product is very large. If the efficacy and safety of this mite bait product can be confirmed for allergic diseases via this test, the product will provide a new tool for the treatment of such allergic diseases in the future.

Additionally, the random grouping, double-blind, crossover test method adopted in this study reduces the influence of selection bias, measurement bias, and other errors on the test results. Each subject will receive two schemes successively, which allows before-and-after comparison, eliminating individual differences while allowing inter-group comparison.

However, due to the long period of this study, problems, such as loss to follow-up, exit, and decline in compliance, may easily occur. Ensuring that each case is in the same condition in each phase of treatment is difficult.

To improve study compliance, we will contact the parents or guardians through WeChat during the study and receive the questions raised by them in real time. Parents and guardians will give consent for the collection of indoor dust mite specimens by staffs who will receive training and provide assessment of the complete specimen collection in strict accordance with sampling procedures. In terms of trial safety, we will track all the events during the study until the incident is alleviated, the situation is stable, other explanations of the incident are obtained, or the contact with the subjects is lost. Subjects are able to drop out of the study at any time and continue to receive standard treatment for rhinitis and asthma in the outpatient department.

In summary, this study will scientifically and objectively evaluate the effect of mite bait on improvement of rhinitis and asthma symptoms, which might provide a convenient means for prevention and treatment of allergic diseases involving the airways in children.

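### The tests named for the crossover are for independent samples and discard the within-child pairing; with positive correlation this is conservative and costs power for moderate effects

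*Protocol article*

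**What the plan says.** Under Trial design, the children have two 8-week treatment phases separated by a 4-week washout: "During this period, the patients will be crossed to accept different interventions for 8 weeks". The Intervention description gives the sequences. Group 1 receives package A and then B. For the other order: "In group 2, package B will be placed for an 8-week intervention, followed by a 4-week washout period", after which package A is placed. This is an AB/BA crossover.

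The statistical methods section then names the tests: "One-way analysis of variance and a two-sample *t* test will be adopted for normally distributed data"; "a non-parametric rank-sum test will be adopted for non-normally distributed data"; and "Fisher’s exact and chi-square tests will be used to compare classified data". It names no paired, repeated-measures or mixed-model method.

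Two other sections bear on the unit of analysis. Sample size: "After crossover, both the placebo and experimental groups will each be increased to 60 people". Unblinding procedure: "the results data will be classified as the test group or the control group for analysis".

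The Discussion gives the reason for the design: "Each subject will receive two schemes successively, which allows before-and-after comparison, eliminating individual differences".

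**The concern.** Each child contributes one active and one placebo period, so the two sets of measurements are correlated. A test for independent samples assumes that they are not. It uses a standard error that includes the between-child variation, which a crossover is meant to remove. The stated analysis therefore works against the stated rationale for the design.

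At stake is the primary comparison of rhinitis VAS, and the secondary comparisons made with the same list of tests. If children who score high in one period tend to score high in the other, the P values are too large, and a moderate real benefit could be reported as no difference because of the test chosen.

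**Working it through.** **Inputs from the protocol article.** Two-sided alpha 5%, power 90%, 44 per group, 10% dropout, 60 children recruited (Sample size). Completers: 60 × 0.9 = 54.

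**Inputs not given, so assumed.** The within-child correlation rho between periods is not stated; I use 0.3, 0.5 and 0.7. Neither the SD nor the baseline mean of VAS is stated, so effects are in units of the SD of a single measurement.

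**The plan's own figure.** Without an SD, 44 cannot be derived independently. Solved backwards for two independent groups, d = sqrt[2 × (1.960 + 1.282)² / 44] = 0.69 (0.70 with the exact t distribution). The same 44 also fits a paired t test with a mean difference of 0.50 SD of the differences, and the text does not say which was used. The dropout step reproduces: 44 / 0.9 = 48.9, so 49.

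**Standard errors.** With n children and unit SD:
- assumed by the two-sample test: sqrt(2/n); for n = 54 this is 0.192
- actual, for the mean within-child difference: sqrt[2(1 − rho)/n]

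The interval width ratio is therefore 1/sqrt(1 − rho), and the actual alpha is 2 × [1 − Φ(1.96/sqrt(1 − rho))].

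| rho | width ratio | actual alpha |
|---|---|---|
| 0.3 | 1.20 | 1.9% |
| 0.5 | 1.41 | 0.6% |
| 0.7 | 1.83 | 0.04% (0.035% before rounding) |

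**Power with 54 completers.** For effect d, the normal approximation gives:
- pooled two-sample test: Φ[(d/0.192 − 1.96)/sqrt(1 − rho)]
- within-child test: Φ[d/(0.192 × sqrt(1 − rho)) − 1.96]

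For d = 0.35 and rho = 0.5, d/0.192 = 1.82. The pooled test has Φ(−0.14/0.707) = 42% and the within-child test Φ(1.82/0.707 − 1.96) = 73%. Simulation with t tests (40,000 runs per cell, 27 children per sequence) gives slightly lower values:

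| rho | 0.35 SD: pooled | 0.35 SD: within child | 0.70 SD: pooled | 0.70 SD: within child |
|---|---|---|---|---|
| 0.3 | 43% | 57% | 98% | 99% |
| 0.5 | 41% | 71% | 99% | 99.9% |
| 0.7 | 39% | 90% | 99.8% | 100% |

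Under no effect, the simulated alpha of the pooled test was 2.0%, 0.6% and 0.04%. A two-sample t test on period differences between sequences held 5.0% to 5.1%.

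**Period.** If the periods differ by a shift s and period is ignored, the bias in the treatment estimate has size s × |n1 − n2|/(n1 + n2), where n1 and n2 are the completers per sequence. It is zero when n1 = n2. As a purely hypothetical case, s = 0.5 SD with 33 and 21 completers gives 0.5 × 12/54 = 0.11 SD. With equal sequences the cost is precision only. At a true effect of 0.4 SD, rho 0.5 and s = 0.5 SD, simulated power is 53% for the pooled test, 76% for a paired test without period and 83% for the period-adjusted test.

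**The case against.** The strongest reply is that the named tests are not wrong in themselves. A two-sample t or rank-sum test on each child's period difference, compared between sequences, is a standard crossover analysis. The unblinding sentence may only describe labelling, since every crossover analysis must label records by treatment, and the sentence about 60 per group may be a headcount. This has some force: the inference rests on several sections read together. But no section mentions within-child differences or a comparison of sequences, and the headcount and the labelling both point to pooled treatment groups. Nor is this a detail left to a separate analysis plan, because the article does name the tests. The absence of period and sequence terms alone would be such a detail; I raise them only because the replacement analysis should carry them.

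A second reply is that the planned effect would be found anyway. That stands if 44 per group came from a two-independent-group formula: at about 0.70 SD the pooled test keeps about 97% power or more.

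Readers might also infer more than the text supports:
- **Inflated false positives.** With positive correlation the error goes the other way, so a significant result would remain credible. Only negative correlation would inflate alpha (7.4% at rho = −0.2).
- **Bias from season.** The documents do not call dust mite exposure seasonal and do not give enrolment timing within the July to June window. A period shift biases the estimate only if the sequences are also unequal.
- **The same fault in the additional regressions.** That section does not state the data structure.
- **Wrong planned confidence intervals.** The methods section mentions only P values; the interval widths above are implied by the tests.

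**Conclusion.** The concern holds. Independent-sample tests are named for paired data, against the design's own rationale. The consequence is conservative error and lost efficiency: actual alpha of about 1.9% to 0.04%, and implied intervals 1.20 to 1.83 times too wide, for an assumed correlation of 0.3 to 0.7. Power for 0.35 SD is about 40% instead of 57% to 90%. That effect is half the planned one only if 44 is a two-independent-group figure. The documents do not support saying that the trial would miss its planned effect or produce spurious positives. Ignoring period adds a loss of precision if the periods differ, and bias only if the sequence groups also end up unequal, for example through dropout.

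**What to change.** For VAS and the other continuous outcomes, replace the named tests by a linear mixed model with treatment, period and sequence as fixed effects and child as a random effect. Alternatively, keep the two-sample t or rank-sum test but state that it is applied to each child's period-1 minus period-2 difference, compared between group 1 and group 2. The mixed model and the t test on differences agree for children with both periods complete. For binary outcomes, use a matched method that allows for period, such as Mainland-Gart or conditional logistic regression.

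The cost is rewording of the statistical section, with no extra data, visits or children. The stated end date (28 June 2020) precedes publication (29 July 2020), so the change should be dated and documented before unblinding.

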### Concealment mechanism

Random sequences will be successively assigned to the subjects according to the enrolment order.

Odd-numbered subjects will be entered into group 1, and even-numbered subjects will be entered into group 2. Three copies of the generated distribution sequence table will be distributed among the designer, pharmacist, and statistician. Each copy will be sealed in an opaque envelope and kept under lock.

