### Interim analyses

At the end of the first phase of the test (V3), an interim analysis of the data from the previous stage will be conducted by the biostatistician of the data monitoring committee, who will primarily analyse the size of the estimated effect in advance and the incidence of adverse events. If there is a lack of treatment effect or the incidence of adverse events is high, early termination of the trial will be considered. These results will be reported back to the trial sponsor, and he or she will decide whether to terminate the experiment or not.

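### The named tests leave out the V1 VAS score, which costs precision in period-1 comparisons and above all at the V3 interim of about 30 versus 30 children

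*Protocol article*

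**What the plan says.** **Outcome and timing.** The primary outcome is the VAS score for rhinitis symptoms over the previous week (Outcomes, Primary outcome). RCAT and ACQ-5, by contrast, are listed as changes. Symptom scores are collected at V1 to V7 (Intervention description). V1 is the first day after enrolment, V3 is week 8 and V4 is week 12, when period 2 starts (Trial design).

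**Tests.** Statistical methods for primary and secondary outcomes names "One-way analysis of variance and a two-sample" t test for normally distributed data and a rank-sum test otherwise. Methods for additional analyses mentions regression only for factors that affect disease control, not for the treatment comparison.

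**Interim.** At V3, "an interim analysis of the data from the previous stage will be conducted". It looks mainly at the size of the estimated effect and at adverse events. If treatment effect is lacking, termination will be considered and the sponsor decides. No test or threshold is given.

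**Size.** The starting point is "Based on the assumption that a reduction of 25% in VAS scores would be of clinical significance", and "enrolment of 44 patients in each group is required at the 5% significance level (two-tailed), with a power of 90" per cent. Then "Considering a 10% possible dropout rate, at least 49 people need to be enrolled in each group". The trial recruits 60 children, and after crossover "both the placebo and experimental groups will each be increased to 60 people". On allocation: "Odd-numbered subjects will be entered into group 1, and even-numbered subjects will be entered into group 2".

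**The concern.** At V3 only period 1 has been observed, so no child yet serves as its own control and the comparison is between two separate groups of about 30. The V1 score is the obvious source of extra precision. It refers to the week before the visit and is taken on the first day, so it cannot reflect an effect of the bait. A test without a baseline term leaves that information unused at a look that can end the trial.

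The Discussion says that the design allows before-and-after comparison and removes individual differences. The tests named for the treatment comparison do neither.

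**Working it through.** **Inputs from the protocol article.** Two-sided 5% level, 90% power, 44 per group, 25% reduction, 10% dropout, 60 children (Sample size). Odd/even assignment gives about 30 per group in period 1.

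**Assumptions.** No VAS mean, SD or correlation is given. V1-V3 correlation r is taken as 0.3, 0.5 and 0.7.

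**1. The plan's own figure.** The dropout step reproduces: 44/0.9 = 48.9, so 49. The 44 cannot be derived from the text because no SD is stated, but it can be inverted:

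d = (1.960 + 1.282) × √(2/44) = 0.691, or 0.699 with the t distribution.

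If the 25% is relative to the mean, the SD is 0.25/0.691 = 0.36 of that mean.

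**2. Interim at 30 versus 30.** In SD units the unadjusted SE is √(2/30) = 0.258. With V1 as covariate it is multiplied by √(1 − r²). The half-width is 1.96 × SE. Power, if p<0.05 were the criterion, is Φ(0.691/SE − 1.96). Simple change scores have SD √(2(1 − r)).

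| Analysis | CI half-width (SD) | Power | Equivalent unadjusted n per group | Power with change scores |
|---|---|---|---|---|
| Unadjusted | 0.51 | 76% | 30 | – |
| V1 covariate, r = 0.3 | 0.48 | 80% | 33 | 62% |
| V1 covariate, r = 0.5 | 0.44 | 87% | 40 | 76% |
| V1 covariate, r = 0.7 | 0.36 | 96% | 59 | 93% |

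With 27 versus 27 (10% dropout), power is 72% unadjusted and 83% at r = 0.5. Change scores do worse than raw scores at r = 0.3 and only equal them at r = 0.5, so the method should be named as ANCOVA.

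**3. The interim read as an estimate.** The text speaks of the size of the effect, not of significance. With d = 0.70, half the design effect is 0.35. The chance that the estimate falls below it is:

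- unadjusted: Φ(−0.35/0.258) = 8.8%
- adjusted at r = 0.5 (SE 0.258 × √0.75 = 0.224): 5.9%

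The unadjusted chance of an estimate at zero or in the wrong direction is Φ(−0.70/0.258) = 0.3%.

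**4. Final comparison, 60 records per treatment from the same 60 children.** Let rb be the correlation between periods and rw the correlation within a period, both assumed.

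- Two-sample SE, pairing ignored: √(2/60) = 0.183 SD.
- Within-child SE at rb = 0.5: √(2 × (1 − 0.5)/60) = 0.129 SD.
- Adding the V4-V1 difference multiplies this by √(1 − c²), where c = (rw − rb)/(1 − rb). At rw = 0.5, 0.6 and 0.7 the SE is 0.129, 0.126 and 0.118.

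Once pairing is used, leaving out the period baselines therefore makes the SE 0% to about 9% larger (0.129/0.118 = 1.09).

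A simulation of 1,500 trials with an effect of 0.4 SD and rw = rb = 0.5 gave this power: two-sample 61%, two-sample plus baseline 70%, paired 85%, paired plus baseline 85%. Adding baseline to the two-sample test raised its power by shrinking an overstated SE. The true SD of its estimate rose from 0.130 to 0.144.

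**The case against.** **The interim has no significance rule.** This stands. A reader might infer that the unadjusted interim has a 24% chance of wrongly reporting lack of effect. The documents do not support that. The 24% is 100% minus 76% and exists only if non-significance at 5% is taken as lack of effect. On an estimate-based reading the gain is from 8.8% to 5.9%, which is real but modest. Termination is also only to be considered, not automatic.

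**Raw scores are not stated outright.** This also stands. The tests section does not say whether VAS is analysed as a score or a change, and the sample size speaks of a reduction. Raw is the natural reading because the primary outcome is the score while RCAT and ACQ-5 are labelled as changes. If change were meant, baseline would be used, but less efficiently than by ANCOVA.

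**Baselines matter little at the final comparison.** This is correct. It is tempting to blame the final loss of precision on the unused V1 and V4 scores, but almost all of it comes from treating paired records as independent. V4 is also measured after randomisation. The washout is 4 weeks, while adult mites are said to live 4 to 6 weeks (Intervention description). V4 may therefore carry residual period-1 effect, and conditioning on it could shift the estimate.

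**Covariates belong in an analysis plan, and an unadjusted randomised comparison is valid.** Validity is not disputed. But the article does not leave the method open. It names the treatment-comparison tests, and those have no baseline term. Replacing them is a correction to stated text, for efficiency.

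**Conclusion.** The point holds as a loss of precision in between-group comparisons of period 1, chiefly at the V3 interim. At an assumed V1-V3 correlation of 0.5, adjusting for V1 cuts the 95% CI half-width from 0.51 to 0.44 SD, as if each group had 40 children instead of 30. The power figures of 76% against 80% to 96% apply only if p<0.05 is the criterion.

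This rests on four assumptions: the effect of about 0.70 SD back-solved from the sample size, the assumed correlations, a near-equal split of 60 children, and the inference that the stated tests are meant for the interim too.

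It does not extend to a claim that missing baselines are what weakens the final analysis. The main loss there is ignored pairing (SE 0.183 against 0.129 SD at between-period correlation 0.5).

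**What to change.** 1. **V3 interim and any period-1-only analysis:** state that the VAS effect is estimated by ANCOVA of V3 VAS on group with V1 VAS as covariate, reported with its 95% CI.
2. **Final result:** replace the two-sample test by a within-child crossover analysis, either each child's V6-V3 difference compared between sequences or the equivalent mixed model with period.
3. **V4-V1 baseline difference:** use it only in a prespecified sensitivity analysis, not in the main one.

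The cost is analysis wording and about one degree of freedom. V1 and V4 are already collected, so no visit, measurement or child is added.
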